**Fig. 1 Fig1:**
[figure not shown]
Trial flow chart

### Assessment sessions

There will be three assessment sessions (Fig. 1) throughout the programme (week 0, 6 and 10). All three assessment sessions will be identical, except the Oxford Knee Score assessment will be performed in the baseline assessment session (week 0). The WOMAC questionnaire will be assessed at the beginning of each assessment session, after which, reflective markers and EMG electrodes will be attached to the participant. Overground walking, stair ascent and descent, and sit-to-stand will be performed in a block randomised order. All activities will be performed under their preferred overground gait condition, and each activity will be repeated five times. The overground walking speed during each assessment session will be controlled to be within 20% of the baseline overground walking speed. At the end of the final trial of each activity, participants will be asked to report their perceived knee joint pain using NRS.

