### Study population/sample size

A sample size calculation was performed based on randomisation with stratification. Using an alpha level of 0.05, a power of 0.8, and an effect size estimates of 1.01 for KAM based on a previous gait retraining study with a similar design compared to our primary comparison (gait pattern group vs control group) [22]. Given that the comparison between gait pattern group and knee moment group is a secondary objective and no study has done the similar design, we will stick with the sample size needed for our primary objective. Seventeen participants are required for each experimental group. Thus, a total of thirty-four participants are needed to adequately power the study and detect significant differences in KAM between groups. Using a conservative estimate of twenty percent drop-out rate, the aim is to recruit twenty participants per group. For control group, we used an allocation ratio of 2:1 requiring recruitment of ten participants. This unequal allocation ratio for control group has been shown to increase the amount of data in the intervention groups where individual responses are likely more variable [30, 31]. In total, this study will recruit fifty participants.

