### Overview of the programme

Participants in the intervention groups will attend the lab a total of nine times, while the control group will attend a total of seven times. Firstly, all participants will attend the baseline assessment session (week 0a), after which a randomisation procedure will be carried out where participants will be randomly allocated to each group. Then, participants in the intervention groups will attend a biofeedback identification session in the same week (week 0b) to identify their optimal gait patterns. From week 1 to week 6, participants will start the weekly gait training sessions. Intervention groups will have real-time biofeedback along with treadmill walking, while the control group will perform treadmill walking for the same length of time without any instruction or feedback. The last training session (week 6) will finish with the post-training assessment session. Finally, a retention assessment session will be carried out one month later (week 10) for the two intervention groups only. Between the post-training assessment session (week 6) and follow-up assessment session (week 10), there will be no training or instructions of any kind provided. Figure 1 details the trial flow chart.

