#### Knee moment biofeedback gait retraining group

Real-time feedback of their live KAM and KFM graphs along with their visual skeleton will be provided on the screen in front of the treadmill, using the Visual 3D real-time plugin (C-Motion, Inc.) (Fig. 3). During each training session, they will try to reduce the1^st^ peak KAM graph with a target of 10% reduction of their baseline level and not to increase KFM by 1% of their baseline level [33, 34], when modifying their gait patterns (FPA, step width and step length). As such, their optimised gait pattern may change over the six weeks.

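### The week-6 KAM contrast mixes six weeks of training with same-day feedback rehearsal, and a walking-speed difference between arms could add to it

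*Protocol article*

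**What the plan says.** On timing, the Overview of the programme section states: "The last training session (week 6) will finish with the post-training assessment session". The Gait training sessions section sets that bout at 30 minutes of treadmill walking. Feedback takes 24 of those minutes in the two intervention arms; controls walk equally long with none. The Dual-task section adds a Stroop test on the treadmill at the end of every training session, for the intervention arms only, during which they must hold the modified gait. The baseline assessment precedes randomisation, and the week-10 assessment comes after four weeks with no training. The Assessment sessions section nevertheless says: "All three assessment sessions will be identical", with the Oxford Knee Score as the only exception.

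On speed, the same section says: "The overground walking speed during each assessment session will be controlled to be within 20% of the baseline overground walking speed". Participants are assessed in the gait they prefer overground. Step length is one of the three retrained parameters.

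On analysis, the Statistical analysis section bases primary success on the KAM reduction from week 0 to week 6, and Study design makes gait pattern versus control the primary comparison. The printed model contains group, time point, their interaction and a random participant effect. Speed appears only as an exploratory outcome.

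**The concern.** The primary question is what a six-week programme does to KAM. Just before the outcome is measured, the gait pattern arm has rehearsed the target gait under feedback and the control arm has not. A lower week-6 KAM could reflect a learned change, a short-lived after-effect of that day's session, or both. This is the only randomised KAM comparison after baseline, so nothing else in the trial can correct it.

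Speed is a separate route. By controlling speed at assessment the protocol treats it as something that could disturb KAM, but the band is wide. Retraining step length can itself change speed in one arm and not the other, and the printed model would attribute the resulting KAM difference to the intervention without showing how much of it went with speed.

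**Working it through.** **1. Visit count.** Intervention arms: baseline 1 + identification 1 + weekly training 6 + week 10 1 = 9. Controls: baseline 1 + weekly training 6 = 7. Both totals match the Overview, so the week-6 assessment shares a visit with the last bout and controls have no week-10 visit. (The Biomechanical outcomes section reads as if all groups had three assessments. The Overview, the seven control visits and the delayed intervention offered to controls after week 6 all point the other way, and that reading is used here.)

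**2. What precedes each assessment.**

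| Assessment | Gait pattern arm | Control arm |
|---|---|---|
| Week 0 | no training bout | no training bout |
| Week 6 | 30 min treadmill, 24 min of it with feedback, dual task in modified gait | 30 min treadmill, no feedback, no dual task |
| Week 10 | four weeks without training | not assessed |

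Difference between arms just before the week-6 assessment:
- treadmill time 30 − 30 = 0 min, so general exertion largely cancels;
- feedback time 24 − 0 = 24 min, which does not cancel.

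The week-6 between-arm difference is therefore (training effect) + (same-day rehearsal effect): one observed quantity and two unknowns. Week 10 gives only a within-arm change and does not supply the second equation.

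**3. The plan's own scale.** The sample-size section states: "Using an alpha level of 0.05, a power of 0.8, and an effect size estimates of 1.01 for KAM". A two-sided two-sample t calculation at 1:1 gives 16.41, rounded up to 17, in line with "Seventeen participants are required for each experimental group"; power at 17 versus 17 is 0.81. That figure is not disputed here. It shows that the planned effect is 1.01 SD.

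**4. Speed.** Speed = step length × cadence. A 10% shorter step at unchanged cadence gives 0.90 × 1 = 0.90 of baseline speed, which lies inside the 20% band.

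The documents give neither a KAM–speed slope nor a KAM SD, so both are assumptions. With the slope in % KAM per 1% speed, KAM shift = slope × speed difference between arms:

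| Slope (assumed) | 5% difference | 10% difference | 20% difference |
|---|---|---|---|
| 0.25 | 1.25% | 2.5% | 5% |
| 0.5 | 2.5% | 5% | 10% |
| 1.0 | 5% | 10% | 20% |

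Bias in SD units = KAM shift ÷ SD, with the SD assumed to be 20 to 40% of mean KAM:
- low: 0.25 × 5 ÷ 40 = 0.03 SD
- middle: 0.5 × 10 ÷ 30 = 0.17 SD
- high: 1.0 × 20 ÷ 20 = 1.0 SD

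With 20 gait pattern and 10 control participants and no true effect, a two-sided t test at 0.05 would be significant with probability 0.05, 0.07 and 0.70 respectively. The middle case is 0.17 ÷ 1.01 = 0.17, about a sixth of the planned effect.

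**The case against.** The abstract calls the week-6 effect acute and leaves persistence to week 10, so a measure taken soon after training may be what was intended. This stands in part. However, the abstract explains acute as six weeks of training, not as the minutes after one session, and the persistence check has no controls. The gap between bout and assessment is not given, and rest periods may be set out in the full protocol. Rest would shorten the list of worries but would not give controls the same rehearsal.

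Identical may refer only to session content. That is a fair reading, but the text should then say that the preceding activity differs.

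A reader might infer that exertion biases the primary contrast, the pain comparison between arms or the retention analysis. The documents do not support this. Controls walk the same 30 minutes, so only within-arm week 0 to week 6 changes in KAM and pain are mixed with exertion. Retention is judged on week 0 against week 10, and neither follows a bout.

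A reader might also set the speed shift against "a target of 10% reduction of their baseline level". That is the feedback target of the knee moment arm, which is outside the primary comparison. A 20% difference between arms would need one whole arm to walk at the limit of the band while the other did not shift; any common shift cancels.

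Finally, slower walking may be part of how the intervention lowers KAM. This objection stands: speed is not purely a confounder, and adjusting for it answers a different question.

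**Conclusion.** The timing problem holds on the protocol's own text. The week-6 gait pattern versus control contrast cannot distinguish the effect of six weeks of training from same-day rehearsal, and week 10 cannot separate them. The size of the rehearsal part cannot be derived from the documents.

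The speed problem is a possibility, not a demonstrated bias. Under the assumed slopes and a 5 to 20% difference between arms it moves KAM by 1.25 to 20%, or 0.03 to 1.0 SD under the further SD assumption. The middle case is modest: 0.17 SD, with the false-positive chance rising from 0.05 to 0.07. The upper end is a worst case. It would be tempting to conclude that a fixed, tighter limit such as 5% is required. The documents do not support any particular limit, and forcing speed would change what is estimated if speed is part of the effect.

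Overall this is an inexpensive improvement that the trial should make. It does not show that the primary result will be invalid.

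**What to change.** 1. At the week-6 visit, carry out the assessment before that day's treadmill bout, so that it shares the no-bout starting state of weeks 0 and 10. No visit is added. The cost is that the assessment follows five rather than six supervised bouts, which should be stated.
2. Registration was retrospective, so some visits may already be done. For those, state that week 6 measures the effect immediately after a feedback session, and limit the claim about six weeks of training accordingly. Reconcile the Overview of the programme with the statement in Assessment sessions that the three sessions are alike.
3. Prespecify a sensitivity analysis that adds measured overground walking speed as a covariate to the printed week 0 to week 6 model, and report mean speed by arm and time point. Present it beside the unadjusted result, which stays primary, because speed may partly mediate the effect. Speed is already listed as an outcome, so this needs no new measurement.
4. Describe within-arm week 0 to week 6 changes in KAM and pain as taken after exertion wherever the order is not changed.

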### Biofeedback identification session

This session (Fig. 1) will only be conducted in the two intervention groups, and both intervention groups will receive knee moment feedback to identify their optimal gait patterns. Reflective markers and EMG electrodes will be attached. Participants will be instructed to walk on the instrumented treadmill and try various gait patterns (FPA, step width and step length), aiming to reduce the real-time knee moments graphs shown on the screen in front of them. They will first be instructed to try different FPAs, then try different step widths and finally different step lengths, to identify their optimal values for each gait parameter. Then, participants will be given 5 min to explore a combination of gait patterns that can consistently keep the knee moment graphs at a low level, in a symmetric, pain free and sustainable method. This 5-min period will be recorded to identify the FPA, step width and step length that most effectively reduces KAM for each individual.

### Gait training sessions

From week one to week six, participants will attend weekly training sessions to perform constant preferred speed walking on the treadmill. The treadmill walking speed might be different from the preferred overground walking speed during assessment sessions, considering the familiarity and energy expenditure on the treadmill. The constant treadmill walking speed will be set to be 0.1 m/s slower than their choice of preferred speed on treadmill, considering the increased difficulty while interacting with feedback during gait retraining. Training time will gradually increase from 15 min in week 1 to 30 min in week 6 (Fig. 2). For the two intervention groups, real-time biofeedback graphs will be provided with personalised targets while walking on the treadmill. The feedback will be graphical data, not numerical data. The control group will perform treadmill walking for the same length of time without any feedback or instruction. The length of feedback time in the intervention groups will go up by the same amount (three minutes) per week until week 4, while it will remain the same (24 min) from week 5 onwards (Fig. 2).

**Fig. 2 Fig2:**
[figure not shown]
Schedule of training time and feedback time during gait retraining sessions from week 1 to week 6. The orange line represents treadmill walking time, which is identical for all three group. The grey line represents feedback time, which is identical for the two intervention groups

For the participants in the two intervention groups, outside of the lab they will be asked to practice the new gait pattern at least 10 min per day, while also trying to maintain this pattern during the rest of their daily walking. All participants will be given a new weekly activity log and a physical activity monitor at the end of each training session.

#### Knee moment biofeedback gait retraining group

Real-time feedback of their live KAM and KFM graphs along with their visual skeleton will be provided on the screen in front of the treadmill, using the Visual 3D real-time plugin (C-Motion, Inc.) (Fig. 3). During each training session, they will try to reduce the1^st^ peak KAM graph with a target of 10% reduction of their baseline level and not to increase KFM by 1% of their baseline level [33, 34], when modifying their gait patterns (FPA, step width and step length). As such, their optimised gait pattern may change over the six weeks.

**Fig. 3 Fig3:**
[figure not shown]
Example of real-time knee moment feedback (left) and gait pattern feedback (right). The light grey shaded area in each graph is the customised target for each parameter

#### Gait pattern biofeedback gait retraining group

Real-time feedback of their live gait patterns (FPA, step width and step length) graphs with their personalised gait pattern target and their visual skeleton will be presented on the screen in front of the treadmill through the Visual 3D real-time plugin (C-Motion, Inc.) (Fig. 3). The participants individualised gait pattern target will depend on the outcomes from the identification session (week 0b, Fig. 1), which will be the same during each training session. Participants will be told to match the target as much as possible.

#### Dual-task

At the end of each training session for the two intervention groups*,* participants will perform the dual-task (in this case Visual Stroop test), where words that describe a colour (e.g. red, blue) will display on the screen in different colour text (e.g. the word red will be display in blue text), at 2 s intervals. Participants will need to respond with the colour of the text while maintaining the modified gait pattern during treadmill walking.

### Delayed control intervention

While control participants may have a strong preference to receive the intervention, they will be offered a delayed control intervention after they finish the study (Week 6). It will involve a biofeedback identification session and six in-person biofeedback gait retraining sessions.

### Withdraw criteria

Participants will be informed that they are free to withdraw from the study prior to, during and after all data collection sessions. Once the data have been collected, access to change or remove a participant’s data will be limited, as we need to manage information in specific ways for the research to be reliable and accurate. If a participant withdraws from the study, we will keep the already obtained data.

### Statistical analysis

Study outcomes will be assessed quantitatively. The primary outcome will be KAM and KAM impulse, while NRS pain and WOMAC scores will be considered secondary. All other biomechanical outcomes (e.g. spee, EMG data, gait pattern variables) will become exploratory outcome variables in nature. The primary success of the trial will be based on a comparison of KAM reduction between week 0 and week 6, while the success of retention will be based on a comparison of between week 0 and week 10. In the knee moment feedback group, gait pattern changes (FPA, step width and step length) from week 1 to week 6 and 1-month follow-up will be compared to explore the evolvement of the gait pattern in response to knee moment feedback intervention. The proportion of participants adequately completing the programme and the average number of training sessions completed will be reported.

All outcomes will be analysed using the intention-to-treat approach and thus we will include data from all enrolled participants, regardless of dropout. Descriptive statistics will be used to compare participants randomised into the two intervention groups and a control group with respect to baseline variables. Continuous variables will be expressed as the means and standard deviations (if normally distributed). The data normality and sphericity will be tested using Shapiro–Wilk test and Mauchly’s test respectively. Linear mixed effect (LME) models will be used to evaluate whether knee loading variables, knee pain score and WOMAC score significantly differ between the three time points (week 0, week 6 and week 10), with group as fixed effect, and participant (repeat measures) as a random effect. LME will be used for our primary objective to explore the difference between baseline assessment (week 0) and post-intervention assessment (week 6) with comparison of gait pattern group and control group, and the secondary objective to explore the gait pattern difference across all time points in knee moment group. The example LME formula for comparison between the gait pattern and control group within MATLAB is stated as below:$${\text{glme}}\_\mathrm{KAM }=\mathrm{ fitglme}({\text{data}},\mathrm{ ^{\prime}}{\text{KAM}}1 \sim \mathrm{ Group }+\mathrm{ timepoint }+\mathrm{ timepoint}*\mathrm{Group }+ (1|{\text{Participant}})\mathrm{^{\prime}},\mathrm{ ^{\prime}}\mathrm{FitMethod^{\prime}},\mathrm{^{\prime}}\mathrm{Laplace^{\prime}})$$

Where KAM1 is the1st peak KAM; Group is the gait pattern group and control group; Timepoints includes baseline and post-training.

Repeated measures Bland–Altman analysis will be used to test the similarity between gait pattern group and knee moment group [35].

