This study will primarily explore the effectiveness of gait pattern feedback to reduce knee loading and knee pain during a 6-week gait retraining programme, and knee moment feedback group will be exploratory to identify the number of sessions needed to determine the optimal gait pattern over 6 weeks. In a long-term gait retraining programme, the gait patterns identified in the first session may not be optimal due to familiarisation with the environment, skin markers and desired gait alterations, as well as any learning effect or muscle activation adaptations [28]. Therefore, this study will explore if a participant’s optimal gait pattern changes or improves over time when provided with direct knee moment feedback, and how many sessions are required to identify a stable optimised gait pattern. Furthermore, there have not been any studies exploring the translative effect of gait retraining intervention into daily activities other than walking (e.g. sit-to-stand or stair climbing). Addressing these knowledge gaps in the literature will produce quantifiable outcome measures to identify and support the implementation of gait retraining for future clinical rehabilitation in KOA populations.

The primary objective of this study is to compare the effectiveness of gait pattern feedback to a control group, during a 6-week gait retraining programme in a KOA population. The secondary objectives are as follow:Explore the evolvement of gait patterns (FPA, step width and step length) when using knee moment biofeedback over time.Determine the optimal number of knee moment biofeedback sessions to identify the best combination of gait patterns (FPA, step width, step length) and quantify individual differences in the timescale for adaptation.Compare the similarity between gait pattern feedback and knee moment feedback to reduce KAM and pain.Explore and compare the successful internalisation of these two types of biofeedback gait retraining over time, through dual tasks, muscle activation and one-month gait retention.Explore the translative effect of these biofeedback gait retraining programmes on general daily activities.

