### Experimental setting

All sessions will be conducted in the Applied Biomechanics Suite at the University of Bath. During gait retraining sessions, participants will walk on an instrumented treadmill. During assessment sessions, participants will perform overground walking, sit-to-stand and stair climbing on force platforms embedded in the floor and a portable force platform embedded on the first step of a two-step stair. During each session, a twelve camera, three-dimensional optoelectronic camera system (Arqus and Miqus, Qualisys, Sweden) will be used to collect motion capture data. Reflective markers will be placed on the distal phalanx of the first toe, metacarpal phalangeal joints 1 and 5, calcaneus, tuberosity of 5th metatarsal, sustentaculum tali of calcaneus, lateral apex of the peroneal tubercle, medial and lateral malleolus of the ankle, tibial tuberosity, medial and lateral femur epicondyles, left and right anterior superior iliac spine and posterior superior iliac spine, left and right iliac crest, vertebrae C7, suprasternal notch of the manubrium and left and right acromion process. Four marker clusters on rigid plates will be placed on the lateral side of the shank and thigh of each leg. Lower limb muscle activation data will be collected by surface electromyography (EMG), including vastus lateralis, vastus medialis, rectus femoris, biceps femoris, medial gastrocnemius, soleus, tibialis anterior, and gluteus medius.

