#### Biomechanical outcomes

Across all groups, we will collect the biomechanical outcomes measures listed below in all three assessment sessions (weeks 0, 6 and 9). In the intervention groups, we will collect all these measures during training sessions 1 and 6, while training sessions 2–5 will only record knee loading and gait pattern data (no muscle activation data). For the control group, all these measures will only be recorded during sessions 1 and 6.*Knee loading data* will be collected and calculated as KAM, KFM and KAM impulse. Hip moment will also be calculated as exploratory information.*Gait patterns data* will be collected as FPA, step width, and step length. Other gait parameter such as trunk lean and pelvis tilt will also be calculated.*Muscle activations data* will be measured by surface EMG from lower limb muscles using surface electrodes. Before placement, electrode locations on each participant’s affected leg will be palpated, shaved, lightly abraded, and cleaned with an alcohol swab. EMG normalisation will be performed using maximum voluntary contraction (MVC) tests for all these five muscle groups (knee extension, knee flexion, ankle plantar flexion, ankle dorsiflexion, hip abduction).

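### Knee moment group: comparing gait pattern in the training weeks with 1-month follow-up confounds change in the learned pattern with change of surface, speed and feedback

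*Protocol article*

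**What the plan says.** The first secondary objective, at the end of the Background, is to "Explore the evolvement of gait patterns (FPA, step width and step length) when using knee moment biofeedback over time". The Statistical analysis section serves it by stating that, in the knee moment group, "gait pattern changes (FPA, step width and step length) from week 1 to week 6 and 1-month follow-up will be compared". It assigns a linear mixed effects model to "the secondary objective to explore the gait pattern difference across all time points in knee moment group". No term for walking condition is mentioned.

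The walking conditions are described elsewhere in the Methods:

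- Experimental setting, on training: "During gait retraining sessions, participants will walk on an instrumented treadmill".
- Experimental setting, on assessments: "During assessment sessions, participants will perform overground walking, sit-to-stand and stair climbing on force platforms embedded in the floor".
- Assessment sessions: "All activities will be performed under their preferred overground gait condition". Overground speed is held within 20% of its baseline value.
- Gait training sessions: "The constant treadmill walking speed will be set to be 0.1 m/s slower than their choice of preferred speed on treadmill". The same section warns that treadmill and overground speeds may differ.
- Biomechanical outcomes: gait pattern is recorded in every training session of the intervention groups. For the middle weeks the text is that "training sessions 2–5 will only record knee loading and gait pattern data (no muscle activation data"). Those weeks contain no assessment session.

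The last assessment is given as week 10 in most places and as week 9 under Biomechanical outcomes. Week 10 is used below.

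**The concern.** The stated comparison treats weeks 1 to 6 and the 1-month visit as points on one time axis. Three things change together between the training weeks and follow-up: the surface, the rule that sets walking speed, and the presence of live feedback with a personal target. A participant who kept the new pattern could seem to have lost it because free overground walking differs from treadmill walking with a target on screen. Real loss could equally be hidden.

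This matters because it is the only comparison the article names for the gait-pattern variables that includes follow-up. The three-time-point model is specified for knee loading, pain and WOMAC, not for foot progression angle, step width and step length. A reader who wants to know whether the gait pattern persisted would turn to the last step of this series. One-month gait retention is itself among the secondary objectives.

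**Working it through.** The plan states no figure to reproduce, so the check is to trace each time point in the knee moment group to its recording condition.

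| Time point | Session | Surface | Live feedback | Speed rule |
|---|---|---|---|---|
| Weeks 1 to 5 | Training | Treadmill | Yes | 0.1 m/s below preferred treadmill speed |
| Week 6 (a) | Training | Treadmill | Yes, for most of the time | As above |
| Week 6 (b) | Assessment | Overground | None described | Within 20% of baseline overground speed |
| Week 10 | Assessment | Overground | None described | Within 20% of baseline overground speed |

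The three assessments are said to be identical apart from the Oxford Knee Score, so no treadmill or feedback walk is described at week 10.

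**Share of treadmill time with feedback.** Under Gait training sessions, feedback time rises by 3 min a week until week 4 and is 24 min from week 5. Taking the week 4 value as 24 min, feedback time is 15, 18, 21, 24, 24 and 24 min. Training time rises from 15 to 30 min. Equal weekly steps are assumed because the schedule figure is not shown, which gives 15, 18, 21, 24, 27 and 30 min. Feedback then covers 100% of walking in weeks 1 to 4, 24/27 = 89% in week 5 and 24/30 = 80% in week 6, against none at week 10.

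**What each contrast estimates.** Let T(w) be the mean of a gait variable on the treadmill in week w, and O(w) its mean overground.

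- Week 6 from training: O(10) − T(6) = [O(10) − O(6)] + [O(6) − T(6)]. The first bracket is change in the pattern after training. The second is the difference between walking conditions.
- Week 6 from assessment: the step from week 6 to week 10 is O(10) − O(6), which is like for like. The step from week 5 to week 6 becomes O(6) − T(5) = [T(6) − T(5)] + [O(6) − T(6)], so the condition term has moved, not gone.
- Week 1 against follow-up: O(10) − T(1) = [T(6) − T(1)] + [O(6) − T(6)] + [O(10) − O(6)], which is mixed on either reading.

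Weeks 1 to 5 have no overground recording and week 10 has no treadmill recording. No choice of week 6 data therefore makes the series homogeneous.

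**What is not touched.** T(6) − T(1) and the other contrasts among treadmill weeks contain no condition term. If time is a categorical factor, adding a follow-up level does not bias them. O(10) − O(0) and O(10) − O(6) are overground on both sides.

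**The case against.** The strongest reply is that the plan does not call this series a test of retention. The Statistical analysis section gives a separate retention criterion, week 0 against week 10, and both visits are overground. The sentence at issue has a different stated purpose, which is to explore how the pattern evolves. That stands. A reader might infer that the trial's retention conclusion is biased, but the document does not support this.

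A second reply is that the evolution objective, and the question of how many sessions are needed, rest on the contrasts among weeks 1 to 6, which are sound. That also stands. The problem is confined to contrasts that cross from treadmill to overground.

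A third is that week 6 has two recordings and an article may leave the choice between them to a fuller document. This is fair as to which step carries the break. It does not remove the break, because the article itself names the time points and joins them.

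It is also tempting to put a size on the bias. Suppose a speed of 1.2 m/s, a step length of 65 cm and step length proportional to speed to the power 0.4 to 0.5. A 0.1 m/s drop then gives (1.1/1.2)^0.4 = 0.966 to (1.1/1.2)^0.5 = 0.957, a shift of 3.4% to 4.3%, or 2.2 to 2.8 cm. None of these inputs is in the document. The 0.1 m/s is taken from preferred treadmill speed, not overground speed, and participants alter step length on purpose during training. The 20% speed band applies at every overground assessment, so its effect is not a cost of mixing conditions. Nor does the document give the size of the gait modification, so nothing supports saying that the bias is as large.

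**Conclusion.** The point holds in a limited form. As stated, the comparison of training weeks with 1-month follow-up in the knee moment group confounds change in the learned gait pattern with change of surface, speed and feedback. This follows from the session descriptions and needs no assumption about magnitude. It does assume that the week 10 session contains only what the article describes.

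Neither the size nor the direction of the bias can be derived from the document. The analysis sits within one arm (planned n = 20), and the Statistical analysis section classes gait-pattern variables as exploratory. The primary KAM comparison, the week 0 against week 10 retention criterion and the contrasts among treadmill weeks are unaffected. The change should still be made, because the stated contrast could be reported as lost or kept learning when it shows neither.

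**What to change.** Separate the analysis by walking condition in the Statistical analysis section:

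1. Evolution: model foot progression angle, step width and step length from the treadmill training sessions of weeks 1 to 6 only. Remove the 1-month follow-up from this series, and state that the week 6 value is the training-session recording.
2. Gait-pattern retention: in a separate model, use the overground assessments at weeks 0, 6 and 10, reporting week 10 against week 6 and against week 0.
3. Do not interpret a treadmill-to-overground difference as loss or retention of the pattern.

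Adjusting step length for walking speed is at most an optional sensitivity analysis. Speed is itself an exploratory outcome, and adjustment could remove part of a real gait change.

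The cost is a change of wording and one extra model in an exploratory analysis. Every recording needed is already planned, so no visit, measurement or participant is added.
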